### Aim

The aim of the current study is to evaluate the efficacy of CFC therapy on pain in the first 72 postoperative hours of hip fracture patients. The secondary aim is to evaluate the effects on (non-) morphine analgesic use; postoperative hemoglobin level; transfusion incidence; delirium incidence and severity; use of psychotropic medication; length of stay; short-term location and duration of rehabilitation; functional outcome; short-term patient-reported health outcome; general and cryotherapy related complications. Furthermore the feasibility of a cryocompression device on orthopedic/surgery wards is assessed.

We hypothesized that: 1) CFC therapy will lower perceived pain levels and morphine consumption; and 2) will reduce postoperative blood loss and transfusion incidence; and 3) reduced pain by CFC therapy will lead to lower delirium incidence and 4) enhance functional recovery, leading to shorter length of stay in postoperative hip facture patients.

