### Randomization

A balanced 1:1 block (size six) randomization stratified by center will be performed directly after surgery, using Research Manager (RM; version 4.5.0.1), a web-based computer program (Fig. 1). A research nurse who is not involved in the study generates the allocation sequence with RM. Intramedullary hip nail (IMHN), dynamic hip screw (DHS) and cannulated screws are grouped for block randomization, as are total hip arthroplasty (THA) and hemiarthroplasty (HA). The intervention group ‘A’ will receive CFC therapy postoperative; the control group ‘B’ will receive standard care. Due to the nature of the study no blinding can exist as patients, family and physicians notice the use and settings of CFC therapy. Physicians randomize participants with a digital logon to the web-based system or the physician can contact the coordinating investigator and he will randomize the included participant (see Table 1 for criteria).The Informant Questionnaire for the Cognitive Decline in the Elderly (IQ-CODE) questionnaire is administered when the clinician has doubts about the cognitive state that may compromise CFC therapy sessions or study measurements (Table 1). Ideally a MMSE would be used for this purpose, however due frequently perceived pain at the accident and emergency A&E department and consequently administered narcotic analgesics, the hetero anamnestic IQ-CODE is used instead. The coordinating investigator contacts the participating hospitals on a daily basis by telephone or physically to ensure adequate and appropriate enrollment of participants and completeness of data. A list of excluded patients will be drafted.

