### Admission

Patient demographic data are noted on admission as well as American Society of Anesthesiologists (ASA) class, current NRS-pain, delirium observation screening (DOS)-score, activities of daily living (ADL)-Katz score and the New Mobility Score (NMS; Table 4) [44–46]. Time of injury and arrival at the A&E department is noted. Patient delay intervals longer than 6 h are actively explored and reasons for delay are clarified e.g. if a patient was prone and unable to call emergency services.

A standard preoperative venous blood sample is taken in which hemoglobin, hematocrit and mean corpuscular volumes values are measured (Table 4). Upon admission the local hospital analgesic and antithrombotic protocol is started (Table 2). A geriatrician is consulted preoperatively in patients who are older than 70 years and will focus on: polypharmacy, risk reduction of falls, prevention and/or treatment of delirium, optimization of nutritional status. The ADL-Katz score and delirium risk assessment score (DRAS) [47] are completed upon admission; furthermore precipitating factors for delirium (bladder infection and/or retention, fixation, sleep deprivation, electrolyte abnormalities including renal function impairment) are noted throughout the hospital stay. After the operation the surgeon notes the intraoperative blood loss, the type of implant, if applicable intraoperative complications, randomizes the patient and determines the patient’s treatment schedule.

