## Statistics

### Analysis of outcome parameters

All statistical analyses will be computed using the SPSS statistical package (IMB SPSS, Inc., Release 20.0.0.0, 64-bit edition). Statistical analysis will be performed according to the intention-to-treat principle. Baseline characteristics will be described in accordance with CONSORT guidelines [41] using means and standard deviation in case of normal distribution, and medians and interquartile ranges otherwise. Continuous variables will be checked for normality, visually and by using the Shapiro Wilk test. Our primary analysis focuses on the differences in NRS-pain scores between the study groups 24 h postoperative and will be analyzed by use of Student’s T or Mann–Whitney U tests in case of skewed distribution. To assess treatment effect over time, a mixed model analysis for repeated measures will be performed. This model allows missing data and adjustment for serious confounders and interactions. In case of skewed distributions and outliers non-parametric variants will be used (e.g. Mann Whitney U or Friedman tests). Secondary continuous outcome measures (EQ-5D-3L, SF-12, DRS-R-98 and hemoglobin) will be compared by use of Student’s t or Mann Whitney U tests. Ordinal variables will be analyzed using the Mann–Whitney test. Chi-squared tests will be performed in case of categorical variables. In case of important confounding, analysis will be adjusted to correct for these factors (by use of multiple regression analysis, linear or logistic). A *p*-value of < 0.05 will be considered statistically significant.

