Currently three of the four participating hospitals have a geriatric trauma unit, in one of the hospitals with a geriatric trauma unit the care of the surgical geriatric patient is transmitted to the geriatrician in full except for wound assessments and related care. At this ward all patients receive prophylactic haloperidol 1 mg daily, and more if needed. At the hospital without a geriatric trauma unit a geriatrician is not readily available and unable to attend the clinic on a daily basis. Confounding of secondary outcomes as delirium, psychotropic medication and functional outcome can therefore not be ruled out.

When compared to the preoperative values, hemoglobin levels in collected blood samples at postoperative day one are usually much lower than one would expect from the observed blood loss during surgery. This gap called ‘the hidden blood loss’ is thought to arise from, among others gastro-intestinal bleeding [22, 79]. The amount of (hidden) blood loss is more severe when oral anticoagulants or thrombocyte aggregation inhibitors compromise a patient’s hemostasis and this loss may continue throughout the early postoperative period. Hemoglobin measured at postoperative day one is most likely, as opposed to the preoperative values, significantly diluted, thereby underestimating the actual hemoglobin concentration. Combined with the possibility of hidden blood loss throughout the hospital stay, care has to be taken when comparing the value of postoperative day one to day three.

The functional outcome assessment of patients who are not allowed to bear weight at the time of discharge is postponed to the outpatient clinic. At this visit they are allowed to bear weight for the first time in weeks. Testing directly after weight bearing for the first time can introduce confounding.

Finally, care has to be taken to interpret the allocation to rehabilitation facilities. For instance patients who have sufficient family members who can help out at home are more likely to be discharged home with or without homecare rather than be assigned to a rehabilitation clinic or nursing home with rehabilitation facilities.

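### Delirium incidence defaults to an unadjusted chi-squared test, with adjustment only on an undefined trigger, although the randomisation strata and an admission delirium risk score could be fixed as covariates; the centre-confounding caveat needs rewording

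*Protocol article*

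**What the plan says.** - **Hypothesis.** The Aim section states as its third hypothesis that "reduced pain by CFC therapy will lead to lower delirium incidence". Delirium is a secondary outcome.
- **Test.** Analysis of outcome parameters names no test for delirium incidence specifically. As a categorical variable it falls under the general rule: "Chi-squared tests will be performed in case of categorical variables".
- **Adjustment.** The same section continues: "In case of important confounding, analysis will be adjusted to correct for these factors (by use of multiple regression analysis, linear or logistic". It names no covariates and gives no criterion for what counts as important.
- **Allocation.** Randomization states: "A balanced 1:1 block (size six) randomization stratified by center will be performed directly after surgery". It groups nails, screws and plates on one side and arthroplasties on the other for the blocks. The Discussion confirms that surgery type is a stratification factor.
- **Baseline risk.** Admission states: "The ADL-Katz score and delirium risk assessment score (DRAS) [47] are completed upon admission". Table 4 also places DRAS at baseline. The article assigns it no role in any analysis.
- **Caveat.** The Discussion describes hospital differences in geriatric care. Of one geriatric trauma unit it says: "At this ward all patients receive prophylactic haloperidol 1 mg daily, and more if needed". Of another hospital it says: "At the hospital without a geriatric trauma unit a geriatrician is not readily available and unable to attend the clinic on a daily basis". From this it concludes: "Confounding of secondary outcomes as delirium, psychotropic medication and functional outcome can therefore not be ruled out".

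**The concern.** Three statements do not fit together. The design balances centre and surgery group between the arms. The analysis section ignores both by default and admits covariates only if confounding appears. The Discussion then treats centre as a possible confounder of the very comparison that the design protects.

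The trigger is the wrong criterion for these variables. If it means observed imbalance between arms, stratification makes it unlikely to fire for centre, and prognostic variables stay out of the model however strongly they predict delirium. If it means the concern already voiced in the Discussion, it has in effect fired already. The choice between adjusted and unadjusted results therefore stays open until the data are seen, in an open-label trial.

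At stake are some precision for the test of the third hypothesis and a limitation that describes the wrong problem.

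**Working it through.** **1. What the plan powers.** Sample size calculation gives a difference of 1.3, SD 2.2, alpha 5% (two-sided assumed), power 90% and drop-out 22.3%.

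n per arm = 2 × (1.960 + 1.282)² × 2.2² / 1.3² = 60.2, so 61 by the normal approximation and 62 by the t-test. Then 122 / 0.777 rounds up to 158, and 124 / 0.777 = 159.6 rounds up to 160. The stated total of 160 reproduces. It concerns NRS-pain at 24 h; no power is stated for delirium.

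**2. Chi-squared power for delirium.** The control incidence of 45% is the background figure for hip fracture populations. The intervention incidence is an assumption. With mean incidence p̄ and n per arm:

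z = (|p0 − p1| − 1.96 √(2p̄(1 − p̄)/n)) / √((p0(1 − p0) + p1(1 − p1))/n), power = Φ(z).

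For 45% vs 25% and n = 80: (0.20 − 0.1478) / 0.0737 = 0.708, so power is 76%.

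| Assumed incidence on intervention | 80 per arm | 62 per arm |
|---|---|---|
| 35% | 25% | 20% |
| 30% | 50% | 41% |
| 25% | 76% | 65% |
| 20% | 93% | 85% |

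**3. Gain from adjustment.** This was simulated with 3,000 trials per setting and N = 160. There were five sites holding 30, 25, 20, 15 and 10% of patients, two surgery groups, and permuted blocks of six within site and surgery group. Incidence was calibrated to 45% vs 25%. Assumptions not in the documents are the 25%, the site shares, site log-odds offsets reaching ±0.5 or ±1.0, and the AUC of the DRAS-like score. The adjusted analyses use likelihood-ratio tests for arm in logistic models.

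| Site spread | AUC of score | Chi-squared | + centre | + centre, surgery group, score | Full gain (points) |
|---|---|---|---|---|---|
| ±0.5 | 0.50 | 77.2% | 78.6% | 79.0% | 1.8 |
| ±0.5 | 0.65 | 76.0% | 78.0% | 80.6% | 4.6 |
| ±0.5 | 0.74 | 76.5% | 78.0% | 84.2% | 7.7 |
| ±0.5 | 0.81 | 76.1% | 77.3% | 88.8% | 12.7 |
| ±1.0 | 0.50 | 76.8% | 80.6% | 80.6% | 3.8 |
| ±1.0 | 0.65 | 77.2% | 80.3% | 83.4% | 6.2 |
| ±1.0 | 0.72 | 74.7% | 78.3% | 85.4% | 10.7 |
| ±1.0 | 0.80 | 76.5% | 79.0% | 90.1% | 13.6 |

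The simulation error of one power figure is about √(0.77 × 0.23 / 3000) = 0.8 points. Centre alone adds about 1-4 points; the rest depends on DRAS. A separate simulation with 124 evaluable patients, 1,500 trials per setting and no surgery term gave about 65% for chi-squared and 73-78% adjusted, at model AUCs of 0.70 to 0.80.

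**4. Validity.** With no treatment effect and site offsets of ±0.5 or ±1.0, chi-squared rejected in 4.9% and 4.3% of trials. The full model rejected in 5.8% and 5.4%; further null runs ranged from 5.4% to 6.7%. A point or so of the gain in step 3 may therefore reflect a slightly liberal likelihood-ratio test.

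**5. Balance by centre.** In the same simulations the largest within-site difference between arms averaged about 2.4 patients and never exceeded 6. Blocking within strata thus leaves only small incomplete-block differences.

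**The case against.** **Adjustment is already allowed.** A reader might infer that the plan commits delirium to a plain chi-squared test. It does not: logistic regression is permitted, and the Discussion's own remark on confounding could be read as invoking it. This stands. What remains is that the rule, as stated, makes adjustment depend on an undefined condition judged on the data.

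**The covariate list may be in an analysis plan not shown.** That is fair for missing detail. Here, though, the article states a default and a trigger, and both suit stratification factors and a baseline risk score poorly.

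**Nothing is invalid.** A reader might infer that ignoring centre biases the test or inflates type I error. The null results above show no inflation. The issue is efficiency on one of many secondary outcomes, for which the article claims no power.

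**The gain is uncertain.** A reader might take a gain of 6-12 points as established. That holds only for a reasonably predictive DRAS and a 20-point drop in delirium. In a further check with 45% vs 35%, five equal centres and AUCs of 0.50 to 0.73, power rose only from 22-24% to 26-32%, so the comparison stays badly underpowered either way. The simulations also test the arm term by likelihood ratio; they do not evaluate the standardised risk difference recommended here.

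**The caveat is not needless.** A reader might infer that a centre-adjusted model would remove it altogether. It would not. Geriatricians diagnose and grade delirium after a DOS score of three or more, so limited availability at one hospital can affect ascertainment, and a centre term does not recover missed diagnoses. The hypothesis is also worded as acting through pain, and randomisation does not protect that link. The caveat further covers psychotropic medication and functional outcome, which a delirium model does not address.

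**Conclusion.** The concern holds as an inexpensive improvement to a secondary analysis. The default test for delirium incidence is valid but less efficient than a model using the randomisation strata and a baseline score that the trial already collects, and the rule for adjusting is undefined and data-dependent. At 160 patients and an assumed 45% vs 25%, chi-squared power of about 75-77% rises by roughly 2-4 points if DRAS is uninformative and by up to about 13-14 points at an AUC near 0.80. Where the truth lies in that range cannot be settled from the documents.

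The Discussion's conclusion is misnamed. Centre-level care is balanced between arms by design, so it does not systematically confound the randomised comparison. It can still add variance, modify the effect, affect how delirium is ascertained and limit generalisability. The documents support neither calling the planned test invalid nor calling the caveat empty.

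**What to change.** 1. For delirium incidence, pre-specify a logistic model with arm, centre, surgery group and admission DRAS. Define centre as in the randomisation system, since the article counts four hospitals but five sites.
2. Report the standardised (marginal) risk difference with its confidence interval as the main result, because the model's odds ratio is conditional. Keep the raw proportions and the chi-squared test as a supporting table, which also guards against a slightly liberal likelihood-ratio test at this sample size.
3. For this outcome, drop the confounding trigger, so that the covariates do not depend on the data.
4. Reword the Discussion caveat. Say that allocation is stratified by centre, so differences in geriatric care do not systematically confound the comparison between arms. Then name the limits that remain: variance, effect modification, ascertainment where a geriatrician is not available daily, and generalisability.

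The cost is a few sentences and one regression model, made before the data are analysed. No new data are needed.

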## Conclusion

The present study will provide evidence for the efficacy of continuous-flow cryocompression therapy applied after hip fracture surgery. Due to the duplicate trauma this condition encompasses these patients, who are generally aged 70 years and over, are expected to benefit most. Furthermore treatment feasibility is assessed and consequently, recommendations are made about which settings are best to employ.

### Ethics and consent to participate

Permission has been obtained from the 'Medisch Ethische Toetsingscommissie Noord-Holland' regional medical ethics committee (NL45657.094.14) and the trial is registered at www.trialregister.nl on the 23^rd^ of August 2013 with trial number: “NTR4152”. Patients with an intra or extracapsular hip fracture who meet the inclusion criteria and without apparent exclusion criteria (Table 1) are informed about the study both orally and in writing by the assessing physician e.g. the local ward doctor, staff member or consulting geriatricians. Depending on operating room capacity and patient characteristics patients will either first be transferred to the ward or will go directly to the operating room. Patients can be included pre and postoperatively within 6 h post surgery, before the first treatment starts 6 h postoperative (Fig. 1). Maximum time for consideration to participate in the study is set at 12 h. Patients approving to participate need to sign the informed consent form after which baseline characteristics are noted.

### Consent to publish

Not applicable.

### Availability of data and materials

Not applicable as this is a protocol of a study and no data are reported.

## Abbreviations

A&E: accident and emergency
ASA: American Society of Anesthesiologists
CFC: continuous-flow cryocompression
CRF: case report form
DEMMI: de morton mobility index
DHS: dynamic hip screw
DOS: delirium observation screening
DRAS: delirium risk assessment score
DRS-R-98: delirium rating scale revised 1998
EMS: elderly mobility scale
EQ-5D: EuroQol-5D
GRS: game ready system
HA: hemiarthroplasty
IQ-CODE: informant questionnaire for the cognitive decline in the elderly
IRB: institutional review board
MMSE: mini mental state examination
NMS: new mobility score
NRS: numeric rating scale
NSAID’s: non-steroidal anti-inflammatory drugs
PCA: patient controlled analgesia
PROM: patient reported outcome measure
REC: Regional ethics committee
RM: research manager
SF-12: short form-12
SF-36: short form-36
SPPB: short physical performance battery
THA: total hip arthroplasty
TKA: total knee arthroplasty
TUGT: timed up and go test
VAS: visual analogue scale
